## Abstract

Background: Childhood obesity has tripled, reaching critical levels of malnutrition. This factor is directly associated with a poorer health-related quality of life of the child and adolescent population. This article presents the study protocol of the project “Strong schoolchildren with a healthy lifestyle” (EF-Salud), which seeks to analyze the effects of a multicomponent program based on muscle strength exercises, sleep nutritional recommendations, and the use of screens in Chilean educational centers with extremely cold weather. Methods: The study protocol of a randomized controlled trial with a pre- and post-test conducted according to the CONSORT statement is reported. The total sample (*n* = 144) will be schoolchildren from six different school years, four of which will perform an intervention and two control. Intervention group 1 (from two different school years) will receive a muscular strength exercise program in the classroom once a day from Monday to Friday for six months and nutritional, sleep, and use of screens recommendations once a week. Intervention group 2 (from two different school years) will receive a program of nutritional, sleep, and use of screens recommendations once per week for six months. The control group (from two different school years) will carry out their usual school day in relation to physical education classes. Before and after the intervention, the investigators will evaluate the cardiovascular risk, physical condition, and lifestyle related to sleep and use of screens. Expected results: The schoolchildren in intervention group 1 will obtain significant results in increased strength, decreased cardiovascular risk, improved sleep habits, and fewer hours of screen use compared to the other two groups.

## 1. Introduction

Global obesity has almost tripled from 1975 to date [1], reaching unacceptable levels of malnutrition. With more than 38.9 million children overweight and obese [2], it has become the most frequent modern pediatric chronic disease in the world [3]. These conditions have been associated for decades with the development of diseases, such as insulin resistance, type 2 diabetes mellitus, high blood pressure, fatty liver disease [4], and, recently, various types of cancer [5].

In Chile, total obesity (obesity + severe obesity) represents 31.0% of the school population and malnutrition due to excess (overweight + total obesity) 58.3%. The Magallanes Region presents one of the highest levels, with a total obesity prevalence of 33%, the schoolchildren in the fifth grade of primary education being those with the highest total obesity rate (36.3%) [6].

Childhood obesity is directly associated with a poorer health-related quality of life, resulting in greater school absenteeism [7]. In this sense, early detection and treatment of obesity in schoolchildren is the best approach to prevention [8,9]. The strategies that have been carried out for the treatment of obesity and childhood overweight such as modifications to the environment, changes in lifestyle habits [10], and interventions with the family and the educational center are considered effective against this disease [11]. These strategies consist of coordinating physical activities and giving nutritional and lifestyle recommendations within educational establishments [12,13].

Unfortunately, worldwide reports show that more than 80% of the child population does not reach the recommended levels of physical activity [14], and this percentage increases as schoolchildren age [15]. Additionally, the closure of schools and the lack of outdoor activities caused by the recent COVID-19 pandemic [16] affected schoolchildren in their lifestyle [17,18], altering sleep, screen time, diet, and especially physical activity [19]. For this reason, it should be possible to improve lifestyle through educational activities, such as increasing the amount of physical activity during the school day and promoting a healthy lifestyle based on a balanced diet [20,21,22], according to the physical activity recommendations recommended by experts [23].

Strategies such as active breaks correspond to short periods of physical activity of approximately 5 to 12 min carried out inside their classrooms [24]. These school programs promote physical well-being, thus improving physical activity levels, alertness, concentration in the classroom, and academic performance [25,26]. This methodology of the implementation of active breaks is mainly carried out by the teachers of the schoolchildren, using different types of educational strategies [27,28,29].

Over the past decade, there has been growing evidence of the “fat but fit” paradox, in which overweight and fit people have better health indicators and lower cardiovascular risk than healthy-weight, low-fit people [30]. In this regard, there is ample evidence of how physical fitness, and in particular muscle strength training, is being widely recommended by scientific organizations [31], as it is associated with a lower rate of cardiovascular risk factors and with numerous benefits for the physical condition and lifestyles of boys and girls [32,33,34], especially when accompanied by a good diet [35] and an ideal weight [36,37]. Some studies have shown that interventions in which only one intervention component is used seem to have smaller effects than multicomponent ones [38,39]. In fact, although there are many types of interventions in educational centers fighting against childhood obesity linked to malnutrition due to excess [40,41,42,43], inactive lifestyles [44,45], and low adherence to exercise [46,47], it is the multicomponent interventions that precisely combine resistance exercise, nutrition, and the adoption of healthy lifestyles by schoolchildren that show the best results in improving quality of life and physical condition and reducing the cardiovascular risk of children [13,44,48].

To date, according to the literature read, there is no study conducted in Chile that has analyzed the effects of a combined program of muscular strength exercises, eating habits, sleep, and the use of screens. Based on the evidence presented, the following research question arises: What effects provide a combined program of muscular strength exercises and nutritional, sleep, and screen use education on the physical condition, cardiovascular risk, and lifestyles of schoolchildren in the commune of Punta Arenas, Chile? In order to answer the question posed, the following objectives have been proposed:*General objective*

To analyze the effects of a combined program of resistance exercises, nutritional recommendations, sleep, and use of screens in schoolchildren from educational establishments in Punta Arenas.

*Specific objectives (SO)*

**SO1:** To determine the physical condition, cardiovascular risk, and lifestyles at the beginning and at the end of the respective interventions in experimental group 1 (group that will carry out a combined program of muscular strength exercises and nutritional and lifestyle education related to sleep and use of screens), experimental group 2 (group that will carry out nutritional education and lifestyle activities related to sleep habits and use of screens), and the control group (group that will carry out the usual school day concerning physical education classes).

**SO2:** To compare the groups (intragroup differences) and between the groups (intergroup differences) in physical condition, cardiovascular risk, and lifestyles after both interventions.

**SO3:** To determine the benefits of the intervention of experimental group 1 in physical condition, cardiovascular risk, and lifestyles that allow making relevant and evidence-based decisions on the health of schoolchildren.

The following research hypotheses (Rh) are proposed:

**Rh1:** 
*A combined program of muscular strength exercises and nutritional education improves the physical condition, cardiovascular risk, and lifestyles of schoolchildren from educational establishments in Punta Arenas.*

**Rh2:** 
*A combined program of muscle strength exercises, nutritional and lifestyle education related to sleep habits, and the use of screens will present better results in improving physical condition, cardiovascular risk, and lifestyles than just education on nutrition and lifestyle related to sleep habits and use of screens or to only carry out the usual school day of physical education classes of schoolchildren in educational establishments in Punta Arenas.*

## 2. Materials and Methods

### 2.1. Experimental Design

This design (Figure 1) is a study protocol through a randomized controlled trial with a pre- and post-test, following the CONSORT statement [49].

The study is based on the Singapore and Helsinki declarations and all participants will be asked to voluntarily sign a consent form. The protocol was presented to the ethical-scientific committee for human beings of the University of Magallanes and approved with the code N^0^ 005/SH/2023.

### 2.2. Participants

The participants will be students of the 2nd formative cycle (fifth basic year) from two educational establishments in the commune of Punta Arenas, Magallanes Region, Chile. The ages selected for the research correspond to the highest percentage of schoolchildren with obesity and overweight in the region. The sample size will be 144 children (48 for intervention group 1, 48 for the intervention group 2, and 48 for the control group), which was obtained considering 50% heterogeneity, a margin of error of 5%, and a level of 95% confidence. The sample size was calculated a priori using G*Power 3.1.9.7. A total of 132 participants are required (22 in each course) considering α = 0.05, 1-β = 0.8, and an effect size of (ES) = 0.8. Considering the possibility of dropout, 12 more people were added (total *n* = 144; *n* = 24 in each course).

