### 3.4. Randomization

An intentional sample will be carried out with randomization by course of the two selected establishments.

Each educational establishment has three fifth-grade courses each, with similar socio-educational characteristics for their level. The six courses will be randomized (24 subjects per course), of which two courses will represent intervention group 1, two courses will represent intervention group 2, and two courses will represent the control group.

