### 3.7. Statistical Analysis

All analyses will be performed using SPSS v.25 (SPSS, Inc., Chicago, IL, USA). Missing data will be handled by intention-to-treat analysis (multiple imputation method). The description will be made as measures of central tendency and dispersion (continuous variables) and as percentages (categorical variables). Using the Shapiro–Wilk test, the normality of the data will be verified, and a two-step rank transformation will be applied to the non-normal variables. Homoscedasticity will be analyzed using Levene’s test. A 2-way repeated measures analysis of variance (ANOVA) will be used to determine the effects of the interventions. The effects of the model are the group (GE1; GE2; GC), the times (pre-test; post-test), and their interaction over time (time × group). Bonferroni’s post hoc test will be applied to identify statistically significant comparisons. The effect size will be determined using Cohen’s d (<0.2 insignificant; ≥0.2 and ≤0.49 small; ≥0.5 and ≤0.79 moderate; ≥0.8 large), considering *p* < 0.05 and GraphPad Prism v8.

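### The stated 132 and 80% power do not follow from their inputs, the second basis for n is unrelated to the comparison, and neither basis reflects randomisation by course

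*Protocol article*

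**What the plan says.** Section 2.2 (Participants) of the protocol article gives two origins for the sample size.

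- The total of 144, split as "48 for intervention group 1, 48 for the intervention group 2, and 48 for the control group", is said to be one "which was obtained considering 50% heterogeneity, a margin of error of 5%, and a level of 95% confidence".
- A G*Power calculation is then reported: "A total of 132 participants are required (22 in each course) considering α = 0.05, 1-β = 0.8", together with "an effect size of (ES) = 0.8". Twelve children are added for dropout, giving 144, or 24 per course.

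The paragraph does not say which test was sized, which outcome, which effect-size metric, or whether the test is one- or two-sided. The only metric named in the article is in Section 3.7: "The effect size will be determined using Cohen’s d", with 0.8 as the threshold for a large effect.

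Section 3.4 fixes the unit of allocation: "The six courses will be randomized (24 subjects per course"), with two courses going to each of the three groups. Section 3.7 plans a pre/post repeated-measures ANOVA on children, with group, time and their interaction, and no term for course.

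**The concern.** One number cannot come from both a proportion-estimation formula and a power calculation unless the two happen to agree, and here neither reproduces on its stated inputs. Separately, the power calculation counts children as if each had been allocated individually, while the trial allocates six courses. The article prints a specific N, power and effect size, so this is a matter of what is stated, not of detail left to a fuller document.

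At stake is what a reader may take from the 80% figure. The second research hypothesis rests on comparisons between groups, and the abstract and discussion anticipate significant differences between them. A reader will judge any between-group result against a power statement that the design as described does not support.

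**Working it through.** **Inputs.** From Section 2.2: α = 0.05, power 0.8, effect size 0.8, 132 children (44 per arm, 22 per course), 144 after dropout. From Section 3.4: six courses, two per arm. Assumed, because the article does not give them: two-sided testing, the ICC, and the pre-post correlation r.

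**1. The proportion formula.** n = z²p(1−p)/e² = 1.96² × 0.25 / 0.05² = 384.2. At n = 144 the margin is 1.96 × √(0.25/144) = 8.2%, not 5%. With a finite-population correction, n = 144 requires N = 144 × (384.2 − 1)/(384.2 − 144) ≈ 230. No population size is stated.

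**2. The G*Power figure.** Required numbers at α = 0.05 and 80% power (noncentral t and F):

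| Calculation | Required |
|---|---|
| Two-sample t, d = 0.8, two-sided | 26 per arm (power 0.807); 78 for three arms |
| Two-sample t, d = 0.8, one-sided | 21 per arm; 63 |
| Two-sample t, d = 0.8, α = 0.05/3 | 35 per arm; 105 |
| ANOVA, 3 groups, f = 0.8 | 21 in total |
| ANOVA, 3 groups, f = 0.4 | 66 in total (power 0.818) |
| ANOVA, 6 groups, f = 0.8 or 0.4 | 30 or 90 in total |
| Repeated-measures ANOVA, f = 0.8 or 0.4 | 6–30 or 9–78 in total |

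None gives 132. In the other direction, 44 independent children per arm at d = 0.8 have power 0.96 (0.90 at α = 0.05/3), not 0.80. The dropout step is consistent: 132 + 12 = 144.

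**3. Randomisation by course.** With two courses of m children per arm, the difference between two arm means, in SD units, has variance 2 × [ICC + (1−ICC)/m]/2 = ICC + (1−ICC)/m. The noncentrality is therefore 0.8/√(ICC + (1−ICC)/m), on 6 − 3 = 3 degrees of freedom. For m = 22 and ICC 0.05 this is 0.8/√(0.05 + 0.95/22) = 0.8/0.305 = 2.62, giving power 0.44.

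Section 3.7 uses pre and post measurements. A change score has SD √(2(1−r)), so 0.8 raw SD becomes 0.8/0.894 = 0.89 at r = 0.6 and 0.8/0.632 = 1.26 at r = 0.8. The ICC is here applied to the change.

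Power, two-sided 0.05, d = 0.8, 22 per course, 3 df:

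| ICC | No baseline | Change score, r = 0.6 | Change score, r = 0.8 |
|---|---|---|---|
| 0 | 71% | 79% | 96% |
| 0.02 | 57% | 66% | 90% |
| 0.05 | 44% | 52% | 78% |
| 0.10 | 32% | 38% | 62% |

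Keeping all 24 per course changes little: without baseline, 74%, 59%, 45% and 33%. The effect detectable with 80% power without baseline is about 1.3 SD at ICC 0.05 and 1.6 SD at 0.10.

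**The case against.** The strongest reply is that the trial may have 80% power after all, and part of this stands.

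- **The number is generous.** For individually allocated children 132 exceeds every requirement in the second step. A reader might infer that the mismatch leaves the trial too small. It does not; only allocation by course can cause a shortfall.
- **Baseline helps.** The no-baseline column is the pessimistic end, because the plan compares change. At r = 0.8 power is 90% at ICC 0.02; at r = 0.9 it is 96% at ICC 0.05 and 87% at 0.10. A reader might infer that 80% is certainly missed, and the documents do not support that.
- **A design effect alone is milder.** At ICC 0.05 it is 1 + 21 × 0.05 = 2.05, leaving 44/2.05 ≈ 21 effective children per arm and 75% power. Power stays at or above 80% up to an ICC of about 0.04. That calculation assumes degrees of freedom that two courses per arm cannot supply. It is also true that if the ICC were exactly 0, a child-level test would be valid at 96%; the 71% there reflects the 3 df.
- **The metric is unnamed.** If 0.8 were Cohen's f, a class-level F test on 2 and 3 df would have 89% power at ICC 0.05 and 75% at 0.10. But that reading requires only 21 children, further from 132, and does not match the Cohen's d scale of Section 3.7.
- **132 can be reached by changing an input.** Bonferroni at 0.05/3 with d = 0.8 gives 44 per arm at 90% power. The three-group f = 0.4 result is 22 per arm, which might suggest that a per-arm figure was attached to each course. Either is conjecture; the article supports neither.
- **The planned child-level ANOVA has high nominal power.** This does not rescue the claim, because that test does not hold its error rate under clustering. In a simulated two-arm child-level comparison with two courses of 22 per arm, type I error was about 18% at ICC 0.05 and 27% at 0.10.

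**Conclusion.** The point holds as a fault in the stated justification. The proportion formula does not size a three-arm comparison and yields 144 only for an unstated population of about 230. The 132 does not follow from the stated α, power and effect size under any standard calculation tried. The 80% power is unsupported because children are counted as independent although courses are randomised.

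It is not shown that power falls below 80% in every case. For d = 0.8 and a two-sided class-level test, power runs from 32% (ICC 0.10, no baseline) to 96% (ICC 0, r = 0.8) over the tabulated range. In that table 80% is reached only at the high pre-post correlation combined with a low ICC. These figures rest on assumed values of both correlations, on reading 0.8 as Cohen's d in raw SD units, and on 22 children per course.

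**What to change.** In Section 2.2:

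1. Delete the statement based on heterogeneity, margin of error and confidence level.
2. Present n = 144 as six courses of 24, two per arm, not as a size derived for 80% power.
3. Replace the claim that 132 are required with the power, or the detectable effect, of two courses per arm. Name one outcome, the test, its sidedness and the effect-size metric, and give results over a stated range of ICC and pre-post correlation.

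This rewrites one paragraph. It needs no added recruitment and no change to the intervention. The cost is a less favourable stated power.

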### 2.3. Inclusion and Exclusion Criteria

The inclusion and exclusion criteria will be schoolchildren with physical characteristics that allow them to carry out the evaluations (Table 1).

## 3. Procedure

Initial contact will be made with the director of education of the University of Magallanes for project approval and with the directors of the selected educational centers in order to inform them of the objectives and procedures of the intervention.

After having the authorization of the Ethics Committee of the University of Magallanes, the Department of Education, and the directors of the educational centers, training will be carried out for the research group to unify the data collection protocol and the intervention. Then, the teachers of the educational center will be trained, giving them all the information about the project, manuals, and guidelines for the activities to be carried out. They will receive the Gantt chart (Table 2).

At the end of the training, the schoolchildren will meet to give them a complete description of the project with its objectives and authorizations, and they will be invited to be part of it, for which they must sign an assent form. On the other hand, the researchers will attend a meeting with parents or legal guardians of the educational center in which they will receive all the background of the project, explaining all the steps to follow, objectives, risks, and expected achievements for the students. The researchers will invite them to give permission for the students to participate in the program by signing their consent.

### 3.1. Training for Project Collaborators

A preparation session will be held in which the project collaborators (kinesiologist, nutritionist, and psychologist) will be taught the data collection and test protocols. There will also be a tour of the facilities and they will be shown where the anthropometric tests (gym and room of the establishment) and the tests (computer room of the educational center) will be taken. In addition, the classrooms of fifth-grade students will be visited where strength exercises will be carried out and the classrooms where nutritional talks on sleep and the use of screens will be given.

### 3.2. Training for Teachers of the Educational Center

There will be a talk to the head teachers and the subject teachers that fifth-grade students have. Teachers will be instructed with the same information that will be given to schoolchildren, including nutritional recommendations, teaching the types of food intake and caloric expenditure, lifestyle, sleep habits, and screen time. In addition, they will be taught the exercise routine with elastic bands and with their body weight that schoolchildren will perform daily.

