##### Group 2: Nutritional, Sleep, and Use of Screens Recommendations (NSSR)

The nutritional, sleep, and use of screens recommendations will be taught together with experimental group 1, so the application conditions will be the same.

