##### Group 3: Control Group (CG)

The CG will carry out a usual school day in relation to physical education classes.

The program will last six months (Table 3) and will be carried out within the educational centers by a multidisciplinary team [13]. It is expected that this improvement can reduce cardiovascular risk, as has been shown in the literature where overweight children with high muscle strength have fewer cardio-metabolic risk factors than their overweight peers with low muscle strength [32,43,60,61].

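### Section 3.2 trains fifth-grade teachers without limit by arm, which opens a route for contamination of the control and group 2 courses

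*Protocol article*

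**What the plan says.** On who is trained, section 3.2 says "There will be a talk to the head teachers and the subject teachers that fifth-grade students have".

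On content, the same section says "Teachers will be instructed with the same information that will be given to schoolchildren, including nutritional recommendations", and adds that "they will be taught the exercise routine with elastic bands and with their body weight that schoolchildren will perform daily". Section 3 (Procedure) adds materials: "the teachers of the educational center will be trained, giving them all the information about the project, manuals, and guidelines for the activities".

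On the courses, section 3.4 says "Each educational establishment has three fifth-grade courses each, with similar socio-educational characteristics for their level". It randomises all six, so that "two courses will represent intervention group 1, two courses will represent intervention group 2, and two courses will represent the control group".

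On the comparators, the control group section says "The CG will carry out a usual school day in relation to physical education classes", and Table 3 gives control its usual routine in all three rows. The group 2 section says "The nutritional, sleep, and use of screens recommendations will be taught together with experimental group 1". Table 3 gives group 2 its usual routine in place of the strength exercises.

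Table 2 marks teacher training, pre-intervention measurements and randomisation all in March.

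**The concern.** Section 3.2 defines the trained teachers by school grade and not by allocation, while every fifth-grade course is in the trial. A head teacher of a control course would hold all the group 1 content, and a head teacher of a group 2 course would hold an exercise routine that the course is not meant to receive. Nothing asks them to hold it back. The Discussion counts teachers as part of how the programme works: it links adherence to their participation and expects them to encourage healthy habits.

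If some of the content reaches comparator pupils, the differences between arms shrink. The second research hypothesis compares group 1 with group 2 and with the usual school day, so both of its comparisons are exposed. A null result could then mean that the programme does not work or that the comparators received part of it. Without a record of exposure the two could not be told apart.

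**Working it through.** **1. Which teachers are covered**

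- Section 3.4: 2 schools × 3 fifth-grade courses = 6 courses, all randomised, 2 per arm.
- Comparator courses: 2 control + 2 group 2 = 4 of 6.
- Section 3.2 trains the head and subject teachers of fifth-grade students. Read as written, that includes the teachers of those 4 courses.
- No section restricts the training by arm or asks comparator teachers to withhold the content.

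**2. Which content is foreign to which arm**

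| Content taught to teachers | Group 1 | Group 2 | Control |
|---|---|---|---|
| Nutrition, sleep, screens | assigned | assigned | foreign |
| Strength routine | assigned | foreign | foreign |

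**3. Direction of the bias**

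Let L be the effect of the education and E the added effect of the exercise, taken as additive and beneficial. Let a be the share of E that leaks into group 2, a′ the share of E that leaks into control, and b the share of L that leaks into control. The expected differences become:

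- group 1 vs control: (1 − b)L + (1 − a′)E, instead of L + E
- group 1 vs group 2: (1 − a)E, instead of E
- group 2 vs control: (1 − b)L + (a − a′)E, instead of L

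The first two shrink with any leakage. The third shrinks when exercise leaks about equally into both comparators (a ≈ a′). It could move the other way if exercise leaked into group 2 but not into control.

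**4. Size (illustration only)**

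The documents give no contamination rate, so there is no figure of the plan's to reproduce. Inputs from section 2.2: effect size 0.8, α = 0.05, and 132 / 3 = 44 per arm before the dropout allowance. (A two-sided two-sample t-test with these inputs and 80% power needs 26 per arm, or 78 in three arms, so the 132 is not reproduced; this point does not depend on it.) Assumed: a single share c of the difference reaches the comparator, a two-sided test, and children treated as independent. The remaining difference is 0.8 × (1 − c), and the sample size needed for the same power grows by 1/(1 − c)².

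| c (assumed) | Difference (SD) | Power, 44 per arm | Sample size factor |
|---|---|---|---|
| 0 | 0.80 | 0.96 | 1.00 |
| 10% | 0.72 | 0.92 | 1.23 |
| 20% | 0.64 | 0.84 | 1.56 |
| 30% | 0.56 | 0.74 | 2.04 |
| 40% | 0.48 | 0.61 | 2.78 |

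For group 1 vs group 2, c applies to the exercise increment only. These powers ignore clustering by course and are therefore optimistic. Clustering is a separate question and is not counted here.

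**5. Shared premises**

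There are 6!/(2!·2!·2!) = 90 ways to allocate the courses. With three courses per school and two per arm, every school holds at least two arms. Group 1 and control are in different schools only if both group 1 courses are in one school and both control courses in the other: 3 × 3 × 2 = 18 of 90. In the other 72 they share at least one school. The same count holds for group 1 and group 2.

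**The case against.** The strongest reply is that teachers' knowledge is not pupils' exposure. A physical education teacher and a kinesiologist instruct the exercises, a nutritionist and a psychologist give the talks, and co-investigators supervise. No section has comparator teachers deliver anything or gives their courses elastic bands, which three of the four main exercises need. This stands. A reader might infer that the plan as written contaminates the comparators; the documents support only a route for contamination.

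A second reply is that the article uses its terms loosely. Section 3.1 speaks of fifth-grade classrooms where strength exercises take place, which can only mean group 1 rooms, and section 3.2 refers to a daily routine that only group 1 performs. The authors may therefore have meant only the intervention teachers. That is possible, but section 3.2 says who is trained and in what, and the plain reading covers all arms. It is a stated choice, not a detail left to a fuller document.

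Two further inferences are tempting and fail:

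- Table 2 lists training above randomisation, which might suggest that training comes first. Its columns are months, so the order within March is not fixed.
- Three arms in two schools might suggest that every pair of arms shares a building. Some arms always do, but a given pair need not (18 of 90 allocations).

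Finally, the Discussion relies on teachers for adherence, so restricting what subject teachers shared across arms may do has a cost in group 1 as well. This stands, and the fix allows for it.

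**Conclusion.** The point holds as a risk built into the plan. As written, section 3.2 trains the teachers of two control and two group 2 courses in content that their arms are not meant to receive, with no safeguard. The likely bias is toward zero for group 1 vs control, group 1 vs group 2 and group 2 vs control, the last on the assumption that exercise leaks about equally into both comparators.

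The size is unknown. The range of 0.72 to 0.48 SD for 10% to 40% leakage shows only how the difference scales; it is not an estimate. The conclusion rests on the plain reading of section 3.2 together with section 3.4. If the full protocol already trains by allocation, the article needs only to say so. Otherwise the change should be made before the trial starts, because contamination cannot be undone afterwards.

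**What to change.** In section 3.2 and Table 2, state that randomisation precedes teacher training and that training follows the allocation of each course:

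- group 1 course teachers: exercise and education content;
- group 2 course teachers: education content only;
- control course teachers: a description of the project, with the training offered after the post-tests.

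Align the sentence on manuals and guidelines in section 3 (Procedure) with this. Ask subject teachers who work across arms to use the content only in the courses allocated to it. Record any use in non-allocated courses, so that the results can be read against actual exposure.

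The cost is separate short talks instead of one, a set order of steps within March, and somewhat less teacher support where subject teachers are shared, including in group 1 courses. Intervention content, sample size and outcomes do not change.
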